## Abstract

**Background:**

Female volleyball athletes are at high risk of non-contact anterior cruciate ligament (ACL) injuries, particularly during high-impact activities such as single-leg landings after a spike or rapid directional changes. These movements often occur under cognitively demanding conditions, including split attention, fast decision-making, and responses to unpredictable stimuli, which can impair neuromuscular coordination and exacerbate motor deficits, such as dynamic knee valgus (DKV). Although neuromuscular training programs exist, many have not been specifically tailored for female volleyball athletes or integrated cognitive demands mimicking real-game scenarios.

**Objective:**

This study protocol describes a planned randomized controlled trial designed to evaluate the effects of an eight-week neuromuscular-cognitive training protocol in reducing risk factors for ACL injury among female volleyball players with DKV.

**Methods:**

This study protocol describes a two-arm, parallel-group randomized controlled trial that will assess an eight-week neuromuscular-cognitive training program for female volleyball players aged 18–23 with clinically confirmed DKV and competitive experience. Participants will be randomly assigned to either an experimental group that will receive integrated neuromuscular-cognitive training or a control group that will receive standard neuromuscular training without cognitive components. The intervention will combine sport-specific motor tasks with cognitive challenges aimed at improving neuromuscular control and decision-making during dynamic movements. The primary outcome will be single-leg landing kinematics under cognitive and non-cognitive conditions. Secondary outcomes will include cortical brain activity, lower limb muscle activation, single-leg balance, muscle strength, and knee joint proprioception. Additional measures will involve participant feedback on training intensity and satisfaction.

**Discussion:**

If effective, this protocol will provide evidence for integrating cognitive training into ACL injury prevention programs for female volleyball athletes. By examining the interaction between cognitive load and neuromuscular control under sport-specific conditions, this study may contribute to a better understanding of cognitive and neuromuscular mechanisms involved in injury prevention and inform future preventive strategies in sports medicine.

## Background

Volleyball is a high-intensity sport involving repetitive movements such as jumping, rapid landings, and sudden directional changes, which place substantial mechanical stress on the knee joint and the anterior cruciate ligament (ACL) [1,2]. ACL injuries are among the most common and debilitating injuries in female volleyball players, significantly affecting athletic performance, quality of life, and long-term athletic prospects [3–5]. Research indicates that female volleyball players have a higher risk of non-contact ACL injuries compared to their male counterparts. These injuries most commonly occur during single-leg landings after spiking or during sudden defensive movements involving rapid directional changes. Biomechanical studies show that female athletes tend to land with reduced knee and trunk flexion and lower core muscle engagement than male athletes, which may contribute to increased anterior tibial shear force and greater stress on the ACL [1,2].

Abnormal landing patterns, including asymmetric knee joint angles, excessive femoral internal rotation, and increased dynamic knee valgus (DKV), represent high-risk movement profiles associated with ACL injuries [6,7]. Modifiable factors, such as weakness in the trunk stabilizers, quadriceps, and hamstrings, as well as muscle imbalances, further increase this risk [8,9]. Insufficient muscular support forces passive structures, such as ligaments and menisci, to absorb mechanical loads, significantly elevating the risk of injury [9]. To address this issue, screening tools such as the Tuck Jump Test have been developed to identify neuromuscular deficits, including DKV [9].

However, biomechanical and muscular factors alone may not fully explain the mechanisms underlying ACL injury risk. Because motor control relies on the coordinated function of the central nervous system (CNS), recent studies have increasingly emphasized the potential role of CNS function in ACL injury risk [10–12]. Neuroimaging studies using electroencephalography (EEG) and functional magnetic resonance imaging (fMRI) have reported alterations in the activation of brain regions involved in motor control, proprioception, and attention among athletes with characteristics associated with increased ACL injury risk [11,12]. These findings suggest that cognitive factors, such as decision-making, focus, and attentional control, may play an important role in injury prevention [11,12].

In real-game situations, jumping and landing occur under cognitively demanding and unpredictable conditions, requiring rapid decision-making, simultaneous processing of multiple stimuli, and swift motor responses [13]. This phenomenon, known as cognitive-motor interference or dual-task interference, occurs when cognitive demands compete with motor control for limited attentional resources. Cognitive challenges may impair the regulation of complex motor tasks, such as landing, and exacerbate movement deficiencies like DKV [13–16].

However, most existing injury prevention programs, such as FIFA 11+ and the PEP program, primarily focus on physical components, including muscle strengthening, balance training, and landing technique modification, while providing limited emphasis on cognitive domains such as attention, decision-making, and motor planning [17]. As a result, their applicability to cognitively demanding competitive environments may be limited. Thus, a training protocol that integrates neuromuscular performance and cognitive processing offers a potentially valuable approach to reducing ACL injury risk in female volleyball players, particularly those with DKV. Therefore, this study protocol addresses this gap by describing a randomized controlled trial designed to evaluate a neuromuscular-cognitive training program specifically developed for female volleyball athletes.

The primary objective of this trial will be to evaluate the effects of an eight-week neuromuscular-cognitive training protocol on single-leg landing mechanics, specifically peak knee valgus angle and frontal plane projection angle, during dual-task cognitive conditions in female volleyball players with DKV. The secondary objectives will be to assess the protocol’s effects on cortical brain activity patterns during motor tasks, measured by EEG, lower extremity muscle activation patterns during landing, assessed by surface electromyography (EMG), single-leg balance performance under both static and dynamic conditions, lower limb muscle strength (quadriceps, hamstrings, and hip abductors), and knee joint proprioception. Finally, this trial aims to contribute evidence regarding whether integrating cognitive challenges into neuromuscular training results in different outcomes compared with standard neuromuscular training alone, thereby informing future ACL injury prevention strategies in this high-risk athletic population.

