### Outcomes

Participants will first receive detailed information about the study procedures, ethical considerations, and potential risks before providing informed consent and completing a personal information form. They will then undergo standardized instructions and a familiarization session, followed by a warm-up to standardize physical readiness and minimize injury risk. Assessments will be conducted 72 hours before the start of the eight-week neuromuscular-cognitive training protocol (pre-test) and within 72 hours after the final session (post-test) to evaluate its effects on modifiable ACL injury-related risk factors in female volleyball players with DKV. All assessments will take place in the Sports Rehabilitation Laboratory at Bu-Ali Sina University under standardized temporal and environmental conditions, with precise measures to control external variables and ensure accurate evaluation.

The primary outcome is the change in two-dimensional landing kinematics, particularly movement patterns associated with DKV, during single-leg landing under two conditions: with and without a concurrent cognitive task. Secondary outcomes include electrocortical brain activity measured by electroencephalography (EEG), lower limb muscle activity assessed by surface electromyography (sEMG), single-leg balance, lower limb muscle strength, and knee joint proprioception. These measures will determine the intervention’s impact on neuromuscular, cognitive, and biomechanical factors associated with ACL injury risk.

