### Sample size

The sample size was calculated using G*Power software (version 3.1) for a repeated-measures ANOVA (within-between interaction) to detect changes in DKV angle at initial contact. The effect size was derived from the group × time interaction reported for DKV at initial contact in a previous neuromuscular training study with dual cognitive tasks [24] (partial η² = 0.19), converted to an effect size f = 0.48. Based on a significance level (α) of 0.05, statistical power (1-β) of 0.95, and an assumed correlation of r = 0.5 between repeated measures, a minimum total of 18 participants was required. The required sample size was initially determined based on the primary outcome measure (the DKV angle) to ensure sufficient statistical power. To adjust for multiple secondary outcome assessments and an estimated 20% attrition rate, we inflated the target enrollment to 30 participants, who will be randomly allocated in a 1:1 ratio to the intervention and control groups.

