### Data collection methods

To evaluate landing kinematics, electrocortical brain activity, and muscle activity, a single-leg landing test will be administered under two experimental conditions: with and without a concurrent cognitive task. After reflective markers and EMG sensors are placed on the participant’s preferred kicking leg (determined using a ball-kicking test) and the EEG cap is fitted, participants will perform the landing test three times with cognitive load and three times without cognitive load. During the test, frontal-plane knee valgus and sagittal-plane knee flexion angles, as well as trunk flexion and lateral flexion angles, will be captured using two cameras positioned for anterior and lateral views. Muscle activity in the vastus medialis, vastus lateralis, biceps femoris, semitendinosus, and gluteus medius will be measured using surface EMG. Electrocortical brain activity will be recorded via 19 EEG channels at theta and alpha-2 frequency bands [25].

To begin the test, participants will cross their arms over their chest to minimize upper-limb movement while standing on a 30 cm-high step [22]. The heel of the dominant foot will be positioned at the edge of the step to limit preparatory movement. Participants will look forward to a wall-mounted screen. After the presentation of the final arrow cue, the participant will perform a single-leg landing on either the right or left target area marked on the floor, based on the direction of the final arrow. The test will also be conducted without cognitive load as a control condition. If the participant cannot maintain balance or demonstrates loss of control (for example, requires additional support, steps outside the target area, or loses postural stability), the trial will be considered invalid and excluded from analysis [26].

After completing the landing tests, participants will stand on a foot scan platform to perform a 30-second balance assessment under eyes-open and eyes-closed conditions. Subsequently, knee muscle strength (flexors and extensors) and hip muscle strength (abductors and adductors) will be measured using a hand-held dynamometer [17]. Knee joint proprioception at 60° of flexion (non-weight-bearing) will be assessed using a goniometer.

In addition, health-related quality of life will be evaluated before and after the intervention using the SF-12 questionnaire [27]. The analysis criterion for all variables will be the change from baseline values.

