### Statistical methods

Descriptive statistics, including means and standard deviations, will summarize the data. The Shapiro-Wilk test will assess data normality. Baseline characteristics will be summarized descriptively between groups. Repeated-measures ANOVA will be used to evaluate the group × time interaction effect as the primary indicator of intervention effectiveness (training vs. control; pre-test vs. post-test). Pairwise comparisons following significant interactions will be conducted with Bonferroni correction to control type I error. The five secondary outcome domains (cortical brain activity, lower-limb muscle activation, single-leg balance, muscle strength, and knee joint proprioception) will be interpreted as exploratory outcomes and hypothesis-generating findings. Partial eta squared will quantify effect sizes, interpreted as small (0.01), medium (0.06), or large (0.14). All analyses will be performed using SPSS version 27 with α = 0.05 and a 95% confidence level.

Given the modest sample size, supplementary analyses will be conducted. Baseline values will be reviewed descriptively, and if clinically meaningful baseline imbalance is observed, ANCOVA models adjusting for baseline values will be performed as sensitivity analyses. Missing data patterns will be assessed, and linear mixed models with appropriate covariance structures will be considered as sensitivity analyses to evaluate robustness under missing-at-random assumptions. Any meaningful discrepancy between supplementary analyses and the primary ANOVA will be reported and discussed.

To assess clinical significance and intervention effectiveness, minimal clinically important difference (MCID) and minimal detectable change (MDC) will be calculated at a 95% confidence level. The MDC will be derived using the standard error of measurement (SEM), as defined by the following formulas [28]:

$$\begin{array}{c} \text{SEM }=\;{\text{SD}}_{\text{pre}}\;\times \;\sqrt{(\text{1}-\text{ ICC})\;} \end{array}$$

$$\begin{array}{c} {\text{MDC}}_{\%\text{9}\text{5}}\;=\;\text{1}.\text{96 }\times \sqrt{\text{2}\;\times \text{ SEM}} \end{array}$$

$$\begin{array}{c} {\text{MCID}}_{\text{RCI}}=\;\text{1}.\text{96 }\times \;{\text{SD}}_{\text{pre}}\;[\sqrt{\left(\text{2}\times (\text{1}-\text{ICC})\right)}] \end{array}$$

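### The primary outcome differs between sections in variable, time point and condition, and no rule says which test decides the trial

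*Protocol article*

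**What the plan says.** All places are in the Protocol article.

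- **Abstract, Methods:** "The primary outcome will be single-leg landing kinematics under cognitive and non-cognitive conditions".
- **Background, primary objective:** "specifically peak knee valgus angle and frontal plane projection angle, during dual-task cognitive conditions". This is two variables, at least the first taken at its peak, in the dual-task condition only.
- **Outcomes:** "The primary outcome is the change in two-dimensional landing kinematics, particularly movement patterns associated with DKV", assessed "during single-leg landing under two conditions: with and without a concurrent cognitive task". No variable or time point is fixed.
- **Sample size:** the calculation was made "to detect changes in DKV angle at initial contact", and the same section says the number was "based on the primary outcome measure (the DKV angle"). This is one variable at initial contact, with no condition given.
- **Data collection methods:** the landing test records "frontal-plane knee valgus and sagittal-plane knee flexion angles, as well as trunk flexion and lateral flexion angles" in both conditions. The section does not say which angle is primary or whether the peak or the initial-contact value is used. It lists no separate frontal plane projection angle.
- **Statistical methods:** the group × time interaction at α = 0.05 is the main indicator of effectiveness. On multiplicity: "Pairwise comparisons following significant interactions will be conducted with Bonferroni correction to control type I error". The five secondary domains are labelled exploratory; landing kinematics is not among them.

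**The concern.** A trial of 30 athletes with one confirmatory claim needs one identified test that decides it. Here the sections differ on three things at once: peak or initial contact, dual-task only or both conditions, and one, two or an open set of variables. They cannot all be the primary outcome.

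Two consequences follow. First, nothing stated limits how many group × time tests can carry the primary claim: the Bonferroni step starts only after an interaction is already significant, and the exploratory label covers only the secondary domains. Second, the power statement is for the initial-contact angle, whereas the objective and the screening threshold (Screening procedures) use peak valgus. The protocol's 95% power is therefore not shown for the variable in its own objective.

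**Working it through.** **1. The definitions side by side**

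| Section | Variable | Time point | Condition |
|---|---|---|---|
| Background | knee valgus angle; frontal plane projection angle | peak | dual-task only |
| Abstract, Outcomes | landing kinematics, with emphasis on DKV patterns | not stated | with and without task |
| Sample size | DKV angle | initial contact | not stated |

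**2. The protocol's own sample size**

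Inputs (Sample size section): partial η² = 0.19, f = 0.48, α = 0.05, power 0.95, r = 0.5. There are two groups and two times.

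- f = √(0.19 / 0.81) = 0.484, which agrees with 0.48.
- For the within-between interaction, λ = f² × N × m / (1 − r) with m = 2 and degrees of freedom 1 and N − 2. At N = 18, λ = 0.2304 × 18 × 2 / 0.5 = 16.6.
- Power is 0.946 at N = 16, 0.959 at N = 17 and 0.968 at N = 18.

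The smallest even total that reaches 0.95 is 18, so the stated figure reproduces. It applies to one test, on the initial-contact angle.

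**3. How many tests could be called primary**

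- Two: the two variables of the objective, dual-task only.
- Four: the same two variables in both conditions.
- Eight: the four recorded angles × two conditions, only if all four are treated as primary.

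**4. Chance of at least one false positive if any one test counts**

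Under independence it is 1 − 0.95^k:

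- k = 2: 1 − 0.9025 = 9.75%
- k = 4: 18.5%
- k = 8: 33.7%

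The angles come from the same athletes and the same landings, so they will be correlated. The protocol gives no correlation between angles or conditions, so a range is assumed. With two time points the group × time F test is the same as a two-sample t test on change scores. That test was simulated with 12 completers per arm (30 × 0.8 = 24 in total), equal correlation between tests and 60,000 replicates.

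| Tests | ρ = 0.5 | ρ = 0.7 | ρ = 0.9 |
|---|---|---|---|
| 2 | 9.1% | 8.4% | 7.1% |
| 4 | 15.7% | 13.4% | 9.8% |
| 8 | 25.8% | 19.6% | 12.5% |

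**5. Cost of a Bonferroni rule**

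The formula of step 2, with N = 24 and α = 0.05/k, gives power 0.994 uncorrected, 0.9855 for k = 2, 0.9686 for k = 4 and 0.9405 for k = 8. These figures take the protocol's f and r at face value and assume that the same f applies to every variable tested.

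**The case against.** The strongest reply is that the intended outcome is evident. Outcomes stresses patterns linked to DKV, Sample size calls the DKV angle the primary measure, and knee flexion and trunk angles are never named as primary. A journal article also condenses, and an analysis plan that is not shown may settle the detail. The first part stands to this extent: an eight-test primary family is possible under the Outcomes wording but is not stated. The second does not remove the problem, because the article does not omit the primary outcome. It states it several times and disagrees with itself.

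A reader might infer that a false-positive primary result is two to seven times as likely as 5%. The documents do not support that as a fact. Those multiples (9.75/5 = 1.95 and 33.7/5 = 6.7) are the independence values for 2 and 8 tests, and independence is implausible here. They also need a rule that any one significant result counts, and Statistical methods states no success rule at all. If every test had to be significant, there would be no inflation. Nor does that section say that each recorded angle gets its own primary test, and the listed angles and conditions give no count above eight.

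A reader might also take the 18 participants to be miscalculated; step 2 shows that the figure reproduces. Finally, the stated model has no factor for cognitive condition. A group × time test within the dual-task condition answers the objective as worded, so a group × time × condition test is an optional extra and its absence is not part of this error.

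**Conclusion.** The point holds. The primary outcome is defined inconsistently in variable, time point and condition, and no stated rule covers several primary tests. That defect does not depend on any assumed correlation.

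The inflation is conditional: it arises if any one of 2 to 8 tests may count, or if the definition is chosen after the data are seen. The false-positive chance is then at most about 10% to 34% under independence and about 7% to 26% at assumed correlations of 0.5 to 0.9. The upper figures apply only if all four angles in both conditions are primary. The 95% power is stated for the initial-contact angle and is an assumption for any other endpoint.

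**What to change.** Name one primary endpoint and use the same words in the Abstract, Background, Outcomes, Sample size, Data collection methods and Statistical methods. One candidate that keeps the planned analysis is the group × time effect on peak frontal-plane knee valgus angle in the dual-task landing. It is already in the objective and is the screening variable. The frontal plane projection angle, the initial-contact angle, the single-task condition and the other angles then become secondary. Type I error for the primary claim is 5%, with no power lost to multiplicity.

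Alternatively, list the primary tests to be kept and pre-specify a Bonferroni or Holm rule. On the protocol's own inputs, Bonferroni with up to eight tests leaves power of about 0.94 with 24 completers.

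In either case, say in Sample size that the effect size came from the initial-contact angle and is an assumption for the named endpoint. A group × time × condition test may be added as a secondary analysis.

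The cost is wording in six places, settled before the outcome data are examined. The downside is that a significant result on another angle or condition can no longer be reported as primary.

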## Methods

### Study design

This study protocol describes a two-arm, parallel-group randomized controlled trial (RCT) that will employ equal allocation (1:1) to evaluate the effects of an eight-week neuromuscular-cognitive training protocol on ACL injury risk factors in female volleyball athletes with DKV. Ethical approval was granted by the Research Ethics Committee of Bu-Ali Sina University (IR.BASU.REC.1402.076). This study has been registered with the Iranian Registry of Clinical Trials (IRCT20190224042827N5), registration date: 24 March 2024. The protocol integrates neuromuscular training principles [18], a cognitive intervention design model for ACL prevention [19], and the JUMP-ACL framework [20] to concurrently enhance motor and cognitive functions, with the aim of improving athletes’ adaptability in competitive environments where physical skills and rapid cognitive processing are critical. Assessments will be conducted at baseline (pre-intervention) and immediately following the eight-week intervention (post-intervention) to evaluate the protocol’s impact on primary and secondary outcomes.

